## Abstract

**Background:**

Current guidelines recommend the prescription of immune-enriched oral nutritional supplements for malnourished patients before major gastrointestinal surgery. However, the benefit of preoperative immunonutrition is still controversial. This randomized controlled trial aims to evaluate the effect of preoperative immunonutrition on the outcomes of surgery for colon cancer.

**Methods/design:**

Patients with primary colon cancer will be included as study participants after screening. They will be randomly assigned (in a ratio of 1:1) to receive preoperative immunonutrition added to the normal diet (experimental arm) or consume normal diet alone (control arm). Patients in the experimental arm will receive oral supplementation (400 mL/day) with arginine and ω-3 fatty acids for 7 days before elective surgery. The primary endpoint is the rate of infectious complications, while the secondary endpoints are postoperative complication rate, change in body weight, length of hospital stay, and nature of fecal microbiome. The authors hypothesize that the rate of infectious complications would be 13% in the experimental arm and 30% in the control arm. With a two-sided alpha of 0.05 and a power of 0.8, the sample size is calculated as 176 patients (88 per arm).

**Discussion:**

Although there have been many studies demonstrating significant benefits of preoperative immunonutrition, these were limited by a small sample size and potential publication bias. Despite the recommendation of immunonutrition before surgery in nutritional guidelines, its role in reduction of rate of infectious complications is still controversial. This trial is expected to provide evidence for the benefits of administration of preoperative immunonutrition in patients with colon cancer.

**Trial registration:**

Clinical Research Information Service KCT0003770. Registered on 15 April 2019.

## Introduction

Even in the current laparoscopic era, postoperative infectious complications still remain the major concern after colorectal surgery. Surgical stress may cause immunosuppression, resulting in postoperative inflammatory and infectious complications [1]. Rapid recovery of patients in the postoperative period is expected in the absence of complications. Particularly, in surgery for colorectal cancer, postoperative infectious complications, such as anastomotic leakage, are significantly unfavorable because these may lead to omission of adjuvant chemotherapy and poorer oncologic outcomes.

Nutrition plays a key role in recovery after major gastrointestinal surgeries. The nutritional risk rate of cancer patients was reported to be 26 to 76%, higher than that of general patients [2]. Patients with colorectal cancer, especially those with advanced tumor, may have a high nutritional risk due to various symptoms such as anorexia, diarrhea, and intestinal obstruction [3]. Malnutrition is closely related to the clinical results of surgical patients, because it can damage the immune system and wound healing process and degrade respiratory and cardiac functions [2, 4].

Proper perioperative nutritional support may enhance immune function and therefore reduce postoperative complications [1]. In recent years, an enteral diet enriched with immunonutrients such as arginine, ω-3 fatty acids, and glutamine has been used. The present international guidelines recommend that immunonutrition should be given to nutritionally high-risk patients before major oncologic surgeries [5]. These guidelines are based on randomized controlled trials demonstrating a reduction in the rate of infectious complications following the use of preoperative immunonutrition [6]. However, since these randomized controlled trials have been criticized for potential conflicts of interests and the small sample size, the usefulness of preoperative immunonutrition still remains controversial [6].

Therefore, we designed this randomized controlled trial to investigate the effect of preoperative immunonutrition on outcomes of surgery in patients with colon cancer.

## Methods/design

### Study design

This study is a randomized controlled trial investigating the effect of preoperative immunonutrition on outcomes of surgery for colon cancer. This protocol is written in accordance with the Standard Protocol Items: Recommendations for Interventional Trials (SPIRIT) checklist [7].

### Objectives and hypotheses of the study

The primary objective of the present study is to evaluate the impact of preoperative immunonutrition on the rate of postoperative infectious complications in patients with primary colon cancer. As a secondary objective, the study will also assess the relationship between the administration of preoperative immunonutrition and postoperative complication rate, change in body weight, length of hospital stay, and nature of fecal microbiome.

### Study participants

To prove the benefit of immunonutrition, we will enroll primary colon cancer patients who are scheduled to undergo surgical resection. The inclusion criteria will consist of patients with primary colon cancer, patients aged 20–80 years, and those who provide a written consent to participate in the study. The exclusion criteria will consist of patients who need emergency surgery, patients with difficulty in oral intake, pregnant women, and patients planned for ostomy surgery. All enrolled patients will be randomized in a 1:1 ratio into one of the following arms after screening: experimental arm (patients who receive preoperative immunonutrition added to the normal diet) or control arm (patients who receive a normal diet alone) (Fig. 1). Because our institution is a regional cancer center that performs about 300 cases of elective colon cancer surgery annually, we expect that registration will be completed in about a year and a half.

**Fig. 1 Fig1:**
[figure not shown]
All enrolled patients will be randomized in a 1:1 ratio into one of the following arms after screening: experimental arm (patients who receive preoperative immunonutrition added to the normal diet) or control arm (patients who receive a normal diet alone)

### Immunonutrition

Patients in the experimental arm will receive 400 mL/day of preoperative oral supplementation in the form of an immunonutrient-enriched enteral feed (Newcare Omega®) added to the normal diet for seven consecutive days prior to surgery. Newcare Omega® contains high protein, arginine, and ω-3 fatty acids. The detailed composition of the oral supplementation is shown in Table 1. Since the time from randomization to surgery will vary from participant to participant, the start date will be specified so that oral supplements can be taken equally for 1 week prior to surgery.

**Table 1 Tab1:** Composition of oral supplementation

	Amount (per 100 mL)
Energy (kcal)	100
Protein (g)	5.0
Fat (g)	3.0
Carbohydrate (g)	13.75
Arginine (g)	0.25
ω-3 fatty acids (EPA + DHA + ALA)	0.23

*EPA* eicosapentaenoic acid, *DHA* docosahexaenoic acid, *ALA* α-linolenic acid

### Ethics and trial registration

All the participants will be completely informed about the protocol of the study, and a written informed consent will be obtained. The protocol of this study was approved by the Institutional Review Board of Chonnam National University Hwasun Hospital (IRB No. CNUHH-2019-062). This clinical trial was registered in the Clinical Research Information Service (CRIS registration No. KCT0003770; https://cris.nih.go.kr/cris/en/).

### Sample size calculation and randomization

Based on a previous meta-analysis, we hypothesize that the rate of postoperative infectious complications would be 13% in the experimental arm and 30% in the control arm [8]. With a two-sided *α* of 0.05 and a power of 0.8, the sample size is calculated as 176 patients (88 per arm). Since the present study compares only short-term outcomes and is very unlikely to cause inconvenience to participants, we think there will be few dropout and do not consider it in calculating sample size. The formula for calculating sample size is as follows.

$$ n=\frac{{\left({z}_{\alpha}\kern0.5em +\kern0.5em {z}_{\beta /2}\right)}^2}{{\left(\delta -\left|\varepsilon \right|\right)}^2}\left[\frac{p_1\left(1-{p}_1\right)}{k}+\kern0.5em {p}_2\left(1-{p}_2\right)\right] $$$$ \left(\alpha =\mathrm{alpha},\beta =1-\mathrm{power},\varepsilon ={p}_1-{p}_2,\delta =\mathrm{non}-\mathrm{inferiority}\ \mathrm{margin},{n}_1={kn}_2\right) $$

The random assignment will be performed in a 1:1 ratio using computer-generated random numbers. To minimize predictability and selection bias, we will use the maximal procedure for random allocation [9]. Investigators will contact a central randomization center by telephone after the patients are enrolled. Except for one researcher who will be aware of the arm assignment and who will prescribe the oral nutritional supplements, all surgeons and other investigators will be blinded. Owing to the nature of the study, the patients will not be blinded.

### Management and assessment

All participants will receive a second-generation cephalosporin as a prophylactic antibiotic and anti-thrombotic prophylaxis with compression stockings. All patients will undergo surgical resection by a colorectal surgical specialist according to oncological principles, via either a laparoscopic or open approach. Oral intake will be initiated the day after surgery unless obstructive symptoms are reported. The timing of discharge from hospital will be determined by the surgeon, considering achievement of pain control, tolerance of diet, and independent ambulation.

Postoperative complications during 30 days following surgery will be documented and divided into infectious and non-infectious complications. Infectious complications include incisional and organ/space surgical site infection and other infections such as respiratory and urinary tract. Body weight will be recorded at the following four instances: at the time of allocation, the day before surgery, 1–2 weeks after surgery, and 1 month after surgery. A fecal microbiome test will be conducted on 32 consecutive patients among all participants. Samples for the fecal microbiome test will be collected in the hospital a day before the surgery. The detailed schedule of assessments is depicted in Table 2.

**Table 2 Tab2:**
[figure not shown]
Schedule of assessments

### Fecal microbiome

A total of 32 feces samples will be collected from 16 patients in each group. We will use the QIAamp DNA Stool MiniKit (Qiagen®, Hilden, Germany) to extract genomic DNA from bacteria in the feces, in accordance with the manufacturer’s instructions. Fecal samples will be mixed with 1.4 mL ASL buffer in a 2-mL microcentrifuge tube and will be vortexed. After centrifuging, a 1.2-mL aliquot of the supernatant will be transferred to a new tube, vortexed with an InhibitEX tablet, and centrifuged. The supernatant will be transferred to a new microcentrifuge tube, mixed with 200 μL AL buffer and 15 μL proteinase K and vortexed, and then centrifuged.

The library preparation will be performed following the 16S Metagenomic Sequencing Library Preparation Illumina Protocol. The V3-V4 region of the 16S rRNA will be amplified. Polymerase chain reaction (PCR) will be performed in a total volume of 25 μL containing 2.5 μL of genomic DNA, 5 μL of each primer, and 12.5 μL of KAPA HiFi Hotstart readyMix. PCR will be conducted by performing 25 cycles of denaturing at 95 °C for 30 s, annealing at 55 °C for 30 s, and elongation at 72 °C for 30 s. Following the completion of the first PCR, DNA electrophoresis will be performed and a single amplification product will be checked to verify correct amplification of V4 of 16S rRNA; subsequently, the first clean-up will be performed. The clean-up procedure will be conducted using AMPure XP beads. The second PCR, called index PCR, will be conducted by performing 8 cycles of denaturing at 95 °C for 30 s, annealing at 55 °C for 30 s, and elongation at 72 °C for 30 s. Following the clean-up procedure, the quality of the final library will be checked, and Agilent Bioanalyzer 1000 and Qbit will be utilized to quantify the amount of DNA.

Metagenome will be analyzed using EZBioCloud (ChunLab, Inc.) and BaseSpace (Illumina) platform. Microbial diversity and evenness will be analyzed using Shannon diversity index and Simpson index, and beta diversity will be utilized to identify the correlation between the samples.

### Statistical analysis

Categorical variables will be compared using the *χ*^2^ test or Fisher’s exact test, and continuous variables will be compared using Student’s *t* test. Two-way repeated measures analysis of variance (ANOVA) will be used to compare the change in body weight between the experimental and control arms. Logistic regression will be performed to conduct multivariable analysis. All results will be considered significant at a *p* value of < 0.05. Statistical analyses will be performed using SPSS version 23.0 (IBM Inc., Armonk, NY, USA).

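### Change in body weight is committed to a two-way repeated-measures ANOVA; a baseline-adjusted mixed model would need no sphericity and would keep patients who miss a weight

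*Protocol article*

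**What the plan says.** The abstract of the protocol article lists weight among the secondary outcomes: "the secondary endpoints are postoperative complication rate, change in body weight, length of hospital stay, and nature of fecal microbiome". Under Management and assessment, weight is recorded "at the time of allocation, the day before surgery, 1–2 weeks after surgery, and 1 month after surgery". The Statistical analysis section fixes the method: "Two-way repeated measures analysis of variance (ANOVA) will be used to compare the change in body weight between the experimental and control arms". It adds: "Statistical analyses will be performed using SPSS version 23.0".

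The text does not state that the allocation weight is one of the ANOVA's time levels. That is an inference, but the natural one: an arm-by-time ANOVA on raw weights captures change since allocation only if the allocation weight is a level. The text names no tested term, sphericity correction, baseline covariate or SPSS procedure, and does not say how missing weights are handled.

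**The concern.** The article names the method itself, so the choice can be judged on its own properties.

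- **Sphericity.** The univariate arm-by-time F test is exact only if all pairwise differences between visits have the same variance. Here the gaps are unequal, one visit has a window of 1–2 weeks, and the Immunonutrition section says that time from randomization to surgery will vary between participants. Equal variances are therefore doubtful.
- **Specificity.** With four time levels the interaction has 3 degrees of freedom. It can be significant without showing when, or in which direction, the arms differ.
- **Complete cases.** Classical repeated-measures ANOVA, as usually run in SPSS GLM, excludes a patient who lacks any one of the four weights. Two of the weights fall after surgery, and patients with complications may be more likely to miss them. The loss could then bias the comparison as well as reduce power.

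At stake is the reliability of one secondary comparison.

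**Working it through.** **Inputs.** From the article: 88 per arm, 1:1 allocation, significance at p < 0.05, four weights. It gives no weight SD, correlation, effect or missing rate, so these are assumed below.

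**The plan's own figure.** There is none for weight. The group size used here does reproduce from the primary endpoint's rates with the unpooled superiority formula: (1.960 + 0.842)² × [0.13 × 0.87 + 0.30 × 0.70] / 0.17² = 7.849 × 0.3231 / 0.0289 = 87.75, so 88 per arm.

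**1. Type I error of the arm-by-time F test** (simulated, 88 per arm):

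| Assumed covariance | Epsilon | Uncorrected | Greenhouse-Geisser |
|---|---|---|---|
| Spherical | 1.00 | 5.2% | 5.0% |
| Random walk over unequal gaps | 0.64 | 7.5% | 5.5% |
| Random slopes | 0.53 | 7.1% | 4.5% |
| Baseline SD 10 kg, step SDs 1.0, 1.5, 1.2 kg | 0.55–0.62 | 7.5–8.6% over repeated runs | 5.1–5.3% |

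The multivariate arm-by-time test, which needs no sphericity, rejects 5.2% in the last setting.

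**2. Does the covariate matter?** Take compound symmetry with correlation ρ and a constant effect at the three later visits. In units of σ², the per-patient variances are:

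- mean of the three later weights: (1 + 2ρ)/3
- change from allocation: (1 + 2ρ)/3 + 1 − 2ρ
- baseline-adjusted: (1 + 2ρ)/3 − ρ²

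At ρ = 0.9 these are 0.9333, 0.1333 and 0.1233. The effect giving the adjusted analysis 80% power is d = 2.802 × √(2 × 0.1233/88) = 0.148σ. The interaction's noncentrality is (88/2) × 0.75d²/(1 − ρ) = 33 × 0.0220/0.1 = 7.26 on 3 and 522 df, which gives 60% power. Across correlations:

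| ρ | Baseline-adjusted | Change score | 3-df interaction |
|---|---|---|---|
| 0.5 | 80% | 60% | 43% |
| 0.7 | 80% | 69% | 52% |
| 0.9 | 80% | 77% | 60% |
| 0.95 | 80% | 79% | 62% |
| 0.98 | 80% | 79% | 63% |

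At the high correlations likely for weight over a few weeks (an assumption), adjustment beats a change score by only 1 to 3 points. The gap to the interaction comes mainly from testing 3 df instead of 1.

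**3. Which contrast?** Power was simulated with baseline SD 10 kg, step SDs 1.0, 1.5 and 1.2 kg, and arm differences at the preoperative, 1–2 week and 1 month visits as shown:

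| Effect (kg) | Greenhouse-Geisser interaction | Multivariate interaction | Average of three visits, baseline-adjusted |
|---|---|---|---|
| 0.5, 0.5, 0.5 | 35–38% | 78–79% | 60–62% |
| 0.5, 0.25, 0 | 33% | 90% | 20% |
| 0.5, 0, 0 | 36–37% | 92–93% | 11–12% |

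In the first scenario a plain change score has the same power as the baseline-adjusted average. Baseline-adjusted preoperative weight alone has 90–91% in the first and third.

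**4. Complete-case loss.** With 5% missing at each of the two postoperative visits, 1 − 0.95² = 9.75%, or about 17 of 176. With independent missingness q at all three later visits, 176 × [1 − (1 − q)³] gives about 5, 10, 25 and 48 patients at q = 1%, 2%, 5% and 10%.

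**The case against.** The strongest reply is that one sentence in an article names a standard method for a secondary endpoint, and the rest is analysis-plan detail. Much of this stands.

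- A reader might infer that the plan will report an inflated test. It does not say so. A Greenhouse-Geisser correction or the multivariate test stays within repeated-measures ANOVA, restores about 5%, and is commonly left to the analysis plan.
- A reader might infer that the plan states that patients with a missing weight are dropped. It does not. Exclusion follows from the usual SPSS procedure, and the sample-size section expects few dropouts.
- A reader might infer that the baseline is wasted. It is not: the interaction uses the allocation weight as the reference for change, and the covariate adds little at high correlation.
- A reader might point to the arm main effect over all four weights, with only 6 to 12% power at ρ = 0.9 to 0.98. But the plan speaks of comparing the change, which in this ANOVA is the interaction. Nothing says the main effect will be used.
- On power alone the ANOVA family is not inferior: in the assumed scenario with a constant effect, its multivariate test (78–79%) beats a baseline-adjusted visit average (60–62%).

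What the reply does not remove is that the article commits to the method. The corrected and multivariate versions repair sphericity but, as usually run, still need all four weights from every patient.

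**Conclusion.** The point holds as a minor but worthwhile improvement. The named method depends on sphericity unless corrected (about 7–8% type I error under the assumed covariances, about 5% after correction), gives an unspecific 3-df answer, and in its usual implementation discards incomplete patients. Of these, the complete-case restriction matters most, because a sphericity correction does not cure it. Its size is uncertain: about 5 to 48 of 176 patients for 1–10% missing per later visit, and whether it biases the result depends on whether missed weights go with complications, on which the article has no data.

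The magnitudes are illustrations under assumed SDs, correlations, effects and missing rates. They do not show that the planned analysis is invalid or that the baseline is thrown away. The primary endpoint, infectious complications, is unaffected.

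**What to change.** Replace the ANOVA sentence with one that specifies a linear mixed model (SPSS MIXED): the three post-allocation weights as outcomes; allocation weight as covariate; arm, visit and arm-by-visit as fixed effects; unstructured covariance; every participant with at least one later weight included. Report the arm difference at each visit with a 95% CI.

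Pre-name one test: either a joint test of the arm differences over the three visits, or the difference at one visit chosen from the expected effect pattern. Do not adopt the visit average by default. Supplementation is given before surgery, so a fading effect is plausible (an assumption), and step 3 of the working shows the average then falling to 11–20% power.

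The cost is one sentence, with the same data and software, settled before any comparison of weights by arm. There are trade-offs. The model assumes that missing weights are missing at random given the observed ones. A joint test still has 3 df, so the visit-specific intervals must carry the interpretation. A single chosen visit can miss an effect elsewhere.

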### Data monitoring

A committee will be organized for trial supervision. The entire process of data collection, recording, and management will be monitored by them. The committee may recommend and request the principal investigator to make some changes to the plan.

### Safety evaluation and reporting of adverse event

Adverse events and serious adverse events should be reported to protect the patient. Serious adverse events which could result in death or life-threatening will be reported within 24 h from the detection by investigators. If there are any adverse events caused by the treatment of the clinical trial, compensation shall be made to the participants by our institution according to the prescribed rules.

### Protocol amendments

If needed, the protocol may be modified by communication and agreement of the principal investigator and trial participants. Revised protocol will be approved by the Institutional Review Board.

### Confidentiality

All study-related information will be safely stored at the study site. All participants’ information will be stored in a locked file cabinet in an area with limited access.

### Reporting of the study results

The results of the study will be released to the participating investigators and patients. The study results will be published regardless of the magnitude or direction of effect.

## Discussion

Infectious complications occur at a relatively high rate (14–27%) following intestinal surgery [8]. Among them, anastomotic leakage is one of the most important infectious complications after surgery for colorectal cancer, which may result in compromised oncologic outcomes. We previously reported that a high nutritional risk screening score was associated with anastomotic leakage after surgery for rectal cancer in our institution [2]. Nutritionally high-risk patients were at two-fold (odds ratio [OR], 2.044; 95% confidence interval [CI], 1.085–3.851; *p* = 0.027) higher risk of anastomotic leakage [2]. Since nutritional risk may be improved by adequate preoperative nutritional support, it may play an important role in reducing postoperative infectious complications including anastomotic leakage.

A few previous studies have reported the benefits of preoperative immunonutrition [10–18]. Regarding colorectal cancer, Moya et al. [18] reported that perioperative use of immunonutrition was associated with decreased wound infection. A recent meta-analysis demonstrated that preoperative immunonutrition was associated with a lower rate of infectious complications compared with no oral nutritional supplementation (OR, 0.46; 95% CI, 0.30–0.83; *p* < 0.01) [19]. Based on this result, current guidelines recommend immunonutrition to be provided to malnourished patients preoperatively [5].

However, despite several previous randomized trials, the number of high-quality trials with a low risk of bias is very small [20]. Furthermore, each of the trials had significant shortcomings such as small sample size [12–15, 17] and possible conflicts of interests [10, 11]. The most notable issue is that industry-funded trials reported a positive effect of immunonutrition [10, 11], whereas a non-industry-funded trial with a large sample size showed no clear advantage of preoperative immunonutrition [16]. These conflicting results suggest that publication bias, which implies a tendency to withhold negative results of trials, may be present [20]. A recent meta-analysis reported that some of the measured significant effects were diminished if the biased trials were excluded [20].

The present well-designed, non-industry-funded, randomized controlled trial is an investigator-initiated study that is free from conflicts of interest. In addition, we will recruit a sufficient number of participants (*n* = 176) to obtain reliable results. Another strength of this study is that we attempt to identify the relationship between immunonutrition and fecal microbiome. In colorectal cancer, the role of microbiome in carcinogenesis and postoperative complications has been studied in various ways, and a recent review suggested that malnutrition may be associated with the deterioration of intestinal microbiome, resulting in a higher incidence of postoperative complications [21]. Through this study, we anticipate to arrive at a more definite conclusion regarding the effect of preoperative immunonutrition in patients undergoing surgery for colon cancer.

